#### Discontinuing criteria

4.2.3

(1)A participant wishing to withdraw from the study for any reason;(2)Serious adverse events or unusual changes in laboratory tests;(3)Patients taking another type of herbal medicine during this study.

### Sample size

4.3

The sample will be calculated based on a previous literature study.^[11]^ The sample size observed in the Vafa's^[11]^ study was calculated on the difference in HbA1C (%) for each person between the initial and final values, resulting in: {mean of differences in the cinnamon group – mean of differences in the control group} / {2 [((SD cinnamon group) 2 + (SD control group 2)/2]} = { –0.44 –(–0.10)}/{2 [(0.722 + 0.652)/2]} = 0.4957 ≅ 0.50. So, if we consider the effect of 0.50, we need 64 participants per group (128 total) for 80% power. Although we do not expect a large loss, if we assume a 20% loss, we will need to recruit about 162 participants to have 130 participants at the end of the study. The calculations were made in GPower 3.0 by choosing the *t* test for independent samples.

### Randomization

4.4

The patients will be distributed into the 2 groups by performing block randomization (n = 6) at a ratio of 1:1 according to a code generated by the statistical package for the social sciences (SPSS) software version 20.0 for Mac (IBM Corporation, Armonk, NY).

#### Allocation

4.4.1

A number will be assigned to each patient, and this number will be labeled on the 3 bottles the patient receives. After this step, the member of the research group returns the box containing all the bottles to the main researcher. When the principal investigator or researchers involved in data collection deliver the vials to the patients, the number contained on the vial will be recorded next to each patient's name.

The registration of the numbers for each patient will be done in written and electronic form. The printed records will be stored in a folder containing the study participants’ documents. Electronic records will be entered into an excel spreadsheet. A copy of the written records will be sent to the study supervisor/coordinator. Each patient's identification number will be listed and registered by the member. This way, the member will know which group each participant will be in.

The list of numbers assigned to each patient will be printed and stored in a sealed envelope, under the responsibility of the member. A copy will be placed in another sealed envelope and will be under the responsibility of the study supervisor/coordinator.

The researcher will also record the data in an excel spreadsheet, save it to a personal computer and include the records in an online “cloud,” with login and password under the researcher's possession only. The lead researcher will only know to which group each participant was assigned at the end of the intervention period.

### Interventions and procedures

4.5

Participants will be allocated into 2 different groups (experimental group and control group). The intervention will last for 3 months, and each participant will receive a total of 3 bottles containing 120 capsules in each bottle of cinnamon or placebo. Each person should take 2 capsules with water 30 minutes before breakfast and 2 capsules 30 minutes before lunch daily for 90 days. A new bottle containing ginger or placebo capsules was delivered at intervals of 25 to 29 days. Participants will be assigned to the experimental (cinnamon) or control (placebo) group at random. Assessments of socioeconomic, clinical, lifestyle, anthropometric, and laboratory variables will be performed in 2 separate visits, like described in Table 1.

(1)Experimental treatment - Cinnamon capsules (*C verum*), at a dose of 3 g/d, and oral antidiabetics.(2)Control treatment – Microcrystalline cellulose capsules (placebo), at a dose of 3 g/d, and oral antidiabetics.

All patients will be encouraged to continue taking their medications routinely, following the recommendations of their attending physicians. Participants will be instructed on how to take the capsules. Both cinnamon and placebo will be encapsulated and packaged in identical vials, containing a label with information on the dosage, expiration date of the product (longer than the intervention period) and the return date. Each vial will be numbered to facilitate participants’ randomization process. To promote participant retention, phone calls will be applied, weekly.

Patients will be encouraged not to change their physical activity or eating routine during the data collection period. All participants will be informed of the risks and benefits of the study and will be aware that they may leave the study at any time for any reason.

After recruitment, evaluation of participation criteria and acceptance of participants to be part of the study, the researchers will set a date to begin data collection. The collection will be divided into 2 steps. In the first stage, participants will be instructed about the study and will collect all socioeconomic, clinical, and laboratory variables. One of the participation criteria will be conditioned to the values of HbA1C. Once the test results are in hand, the principal investigator will schedule a second time with patients in the follow-up health units to be randomized to receive the vials containing the cinnamon or placebo capsules. To evaluate adherence, Morisky test will be applied.

All treatments will be performed by a group of nurses who will undergo a training and calibration exercise in the initial phase of the study. The major researcher will perform the intervention and data collection and will be blind about which group it will conduct.

Blood samples (10 mL) will be taken after 10 to 12 hours of fasting. Samples will be centrifuged at room temperature at 3000 rpm for 10 minutes to separate serum from blood cells. The tests will be determined by the enzymatic colorimetric method with commercially available kits (Pars Azmun Co., Tehran, Iran) on an automated analyzer (Abbott, model Alcyon 300, Abbott Park, IL). In turn, for HOMA-IR, it will be calculated by multiplying the glucose by insulin (μUI/mL), both fasting, and dividing by 22.5, the cutoff established was 2.5.

Venipuncture, manipulation, and analysis of biological samples will be performed by trained professionals and the analysis will be conducted in a CONTROLLAB quality seal clinical analysis laboratory, intermediated by the Brazilian Society of Clinical Pathology and Laboratory Medicine, and the Program quality seal, National Quality Control.

Blood tests results will be delivered to participants after the full study review is completed so that participants do not jump to conclusions about the intervention as well so that they do not start using cinnamon (or not) without awareness of the true efficacy. Between visits, the lead researcher will call participants once every 15 days to follow up on the study. There will be no instruments to complete during these phone calls, but the researcher should record information about the call and related adverse events.

The investigator will analyze, through discussion with the patient, the occurrence of adverse events during each visit, and record the information. Adverse events will be recorded with each participant's instrument and registration number. Adverse events will be described by duration (start and end dates and times), severity, outcome, treatment, and relationship to study drug or, if unrelated, possible cause.

Prior to performing any study-related activities, written informed consent, and authorization must be signed and dated by the patient. If the patient is not literate, the reading of the term will be done by a data collector or the principal researcher, and then the signature will be taken by request. Consent must be obtained prior to performing any study-related collection activities.

After collecting, analyzing data and writing technical documents, the results will be disclosed to patients and professionals who were involved in this study. In addition, the data will be provided to the Brazilian Ministry of Health for future investments in this area.

#### Cinnamon preparation

4.5.1

To produce the cinnamon to be encapsulated will be use the stick, processed in powder form and the final product was cinnamon extract 0.1%. To obtain the raw material extraction will be performed with drying was done by spray dryer of *C verum*. In addition to the physical-chemical test performed by the manufacturer, the microbiological test will be performed, with values within the normal range for counting bacteria, fungi, and yeast, and the purity test with the counting of heavy metals, such as lead, copper, and antimony.

Cinnamon has authorized the use in Brazil and is part of the research exempt from authorization. Therefore, the concept of “Access to Genetic Heritage” available in Provisional Measure 2186–16/2001 does not apply. Remember that this spice has its widespread use in tropical regions of the world.

After the acquisition of cinnamon powder by a specialized industry, the weighing, encapsulation, and repetition of the quality control tests, as physicochemical, will be carried out in a handling pharmacy that has the green quality seal, the excellence in franchising and the Sinamm Diplomation. The weighing will be computed on an analytical balance.

#### Blinding

4.5.2

Due to the objectives of the study, the identity of the test and control treatments will not be known to the principal investigator, data collection team, laboratory analysis laboratory, or patients. The following study procedures will be applied to ensure the triple concealment of study treatments.

(1)Access to the randomization list will be strictly controlled;(2)The capsules, packaging, and labeling of test and control treatments will be identical to maintain confidentiality about the type of treatment;(3)The concentrations of cinnamon or placebo in each capsule will be the same to minimize the breach of treatment confidentiality.

The treatment received by each person will be revealed after the completion of the clinical intervention and after the study database has been completed.

During the study, blinding can only be broken in emergencies when knowledge of the patient's treatment group is necessary for patient management. When possible, the investigator should discuss the emergency with the attending physician before revealing which group the patient is in.

Participants will be disengaged from study medication if necessary, for their safety or if the participant needs emergency surgery and information is requested on all treatment interventions. This is expected to occur very rarely, or never. Only in the event of an emergency where the participant cannot be adequately treated without knowing the identity of the study medication will this be revealed.

In an emergency, the primary care physician where the patient is being followed or the treating physician will be informed if the patient is receiving cinnamon or placebo. If there is no problem with this, the study will move on.

If it is really necessary to “break” the blinding, then the study coordinator/supervisor will contact the study team members responsible for the confidentiality of the randomization information to retrieve the sealed document.

A protocol bypass form must be completed for any event that requires unraveling the participant's assignment.

In the event of blinding “breakage”, the following information will be recorded:

(1)The identification of the participant;(2)The reason for the “break”;(3)The member of the study responsible for the breakage of blinding;(4)A list of people who are no longer blind to the treatment of the person concerned.

#### Monitoring and security

4.5.3

Information on all serious adverse events, adverse events, recruitment, and retention, data integrity and data quality will be available for review by designated research group members. Interim safety analyses will be performed periodically throughout the study. While participant safety is the primary concern of the study, it is difficult to formulate precise discontinuity or interruption guidelines that cover all possible situations that may arise.

Adverse events, particularly severe ones, will need to be carefully considered by the research group regarding treatment group imbalances. There are no safety concerns expected with the drugs administered in this study. Cinnamon has been studied not only by the research group, but by other researchers around the world, so there is no reason to believe that its safety and tolerability are a significant problem. In addition, the group will analyze safety data and ensure the scientific validity and ongoing merit of the study.

#### Protocol violation

4.5.4

Investigators may implement a deviation or change in protocol to eliminate an immediate risk to study participants without prior approval from the ethics committee. As soon as possible, the deviation or change implemented, the reasons for this and, if appropriate, the change (s) to the proposed protocol (s) will be submitted:

(1)To the ethics committee for review and approval/assent;(2)To the analysis group with the members of the research group, if necessary;(3)For the regulatory authority.

#### Data recording and retention

4.5.5

The data will be manually and electronically recorded by the lead researcher in excel, will be shared at the end of the study with 2 researchers who will assist the statistical analysis and control of the data and/or will be checked by 3 separate researchers 1 will check the data entered manually and 2 others will check the electronic data.

To maintain confidentiality, all laboratory samples, evaluation forms, reports and other records will be identified by a coded number and initials only. All study records will be kept in a locked file and code sheets that link the patient name to a patient identification number will be stored separately in another locked file.

Clinical information will not be disclosed without written permission of the participant, except for scientific disclosure (respecting the confidentiality of information such as the name and address of patients) or when necessary for monitoring by the Brazilian Ministry of Health. The researcher must also comply with all applicable privacy regulations.

The database will be protected from unauthorized access by established security procedures (login and password), and appropriate backup copies of the database and files involved in the study will be made. The database will be stored on the main researcher's computer along with any updates. At critical situations of the protocol (eg, interim reporting and final reporting), data for analysis is blocked and cleared according to established procedures. All study documents (patient records, informed consent, etc) will be kept protected for 5 years after the end of the investigation. To ensure data is stored, copies of archives will be archived.

### Statistical analysis

4.6

All variables will be analyzed descriptively, with numerical and visual summaries. The 2 groups will be compared to check for differences in socioeconomic and clinical variables between the 2 groups at baseline. Numerical variables will be analyzed using the *t* test and categorical variables will be analyzed using the chi-square test.

For HbA1c analysis (in%), the change in value from baseline to end of the study will be considered as the primary endpoint and the means of both groups will be compared using the *t* test for independent groups. The significance level for this test will be 0.05. The analysis will follow the intention-to-treat principle, that is, the participant is analyzed in the group to which he was assigned, regardless of completing treatment as prescribed.

Secondary analyses will include means tests (*t* test) for numerical secondary variables, proportional tests for binary secondary variables, and chi-square test for categorical variables with more than 2 categories. Although we continue to use the significance level of 0.05, these tests will be interpreted with caution as the study was not designed to have statistical power for all of these tests. These tests will be considered exploratory.

Depending on the outcome of the primary outcome, exploratory analyzes will incorporate socioeconomic and clinical variables using regression analysis, where the final HbA1c value at the end of the study is the response variable, and the initial value, socioeconomic, and clinical variables, and the group of treatment will be the explanatory variables. Before statistical analysis, we will evaluate the amount and type of missing values. If necessary and possible, we will use multiple imputations to analyze the data. However, we will also perform the analysis with the full data and the final reports will contain the various analyzes so that the reader can compare them (sensitivity analysis).

Statistical analyses will be performed on SPSS version 25 (SPSS Inc., Chicago, IL) and Stata/SE 15.0 (Stata Corporation, College Station, TX) software for data analysis. Graphics will be done in R Studio.

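### Primary test ignores baseline HbA1c, and the baseline-adjusted model is exploratory and run only depending on the primary result

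*Protocol article*

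**What the plan says.** Section 4.6 (Statistical analysis) of the protocol article sets one confirmatory HbA1c comparison. The endpoint is defined by "the change in value from baseline to end of the study will be considered as the primary endpoint". The test is then stated in these words: "the means of both groups will be compared using the *t* test for independent groups". On alpha the section adds: "The significance level for this test will be 0.05". No covariate enters this test. Section 4.3 (Sample size) rests on the same unadjusted comparison of changes: "if we consider the effect of 0.50, we need 64 participants per group (128 total) for 80% power".

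A baseline-adjusted model appears two paragraphs later in section 4.6, in different standing: "Depending on the outcome of the primary outcome, exploratory analyzes will incorporate socioeconomic and clinical variables using regression analysis". The outcome in this model is given as "where the final HbA1c value at the end of the study is the response variable". Baseline HbA1c enters on the other side of the equation: "the initial value, socioeconomic, and clinical variables, and the group of treatment will be the explanatory variables". The article does not say which primary result leads to this model being run, and it does not name the socioeconomic and clinical covariates. Their descriptions in sections 4.1.1.1 and 4.1.1.2 are open-ended. No other part of the article promises a baseline-adjusted estimate whatever the primary result.

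**The concern.** There are two linked problems.

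**Precision.** HbA1c is measured in everyone before randomisation, because eligibility depends on it (sections 4.2.1 and 4.5). A change score fixes the slope of final on baseline HbA1c at 1. ANCOVA estimates that slope. Under randomisation both target the same treatment difference, and with 1:1 allocation ANCOVA is no less precise in large samples. If the true slope is below 1, the change score over-corrects for baseline and leaves the estimate exposed to chance imbalance. Section 4.4 describes blocked randomisation without mention of stratification by HbA1c, so nothing stated there limits such imbalance.

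**Result-dependent analysis.** If the adjusted model is run after a null primary result, it can serve as a rescue analysis. If it is run after a positive one, it is selective confirmation. Because the trigger is not stated and the covariates are not listed, a reader of the final report could not tell whether the data drove the model's presence, absence or content.

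**Working it through.** **Inputs from the protocol article.** Section 4.3 gives mean HbA1c changes of −0.44 and −0.10, an effect of 0.50, 64 per group, 80% power and 20% loss. The SDs of change are 0.72 and 0.65; the printed "0.722 + 0.652)/2]} = 0.4957" is read as 0.72² and 0.65² with lost superscripts. Alpha is 0.05 (section 4.6). Allocation is 1:1 (section 4.4).

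**Assumed.** The baseline-to-final correlation ρ is not given. I take 0.5 to 0.9 and, to begin with, equal SDs at both visits.

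**1. Reproducing the plan's own figure.**
- Pooled SD of change = √((0.72² + 0.65²)/2) = √0.4705 = 0.686.
- Effect = 0.34/0.686 = 0.4957, rounded to 0.50 as stated.
- A two-sided t test at 0.50 needs 63.8, so 64 per group, with power 80.1%. The plan's sample size reproduces. A one-sided test would need only 51, so the plan is two-sided in effect.

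**2. Variance of ANCOVA relative to the change score.** With common SD s:
- change-score variance = 2s²(1 − ρ)
- ANCOVA residual variance = s²(1 − ρ²)
- ratio = (1 + ρ)/2

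The effective standardised difference therefore becomes 0.50/√((1 + ρ)/2).

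**3. Power at the same true effect (noncentral t).**

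| ρ | Variance ratio | Power, 64 per group | N per group for 80% | Power, 52 per group |
|---|---|---|---|---|
| t test on change | 1 | 80.1% | 64 | 71.4% |
| 0.5 | 0.75 | 90.0% | 49 | 83.0% |
| 0.6 | 0.80 | 88.1% | 52 | 80.6% |
| 0.7 | 0.85 | 86.1% | 55 | 78.2% |
| 0.8 | 0.90 | 84.1% | 58 | 75.9% |
| 0.9 | 0.95 | 82.1% | 61 | 73.6% |

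The last column covers one possible reading of the recruitment figures. The Abstract and section 4.1 expect 130 participants in all. If that is the number enrolled, a 20% loss leaves 130 × 0.8 = 104, or 52 per group. Section 4.3 instead recruits about 162 to finish with 130.

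A simulation at 64 per group (4,000 runs per value) agrees. Power for the t test against ANCOVA was 80.7% v 90.1% at ρ = 0.5, 79.8% v 86.0% at 0.7, and 79.6% v 83.4% at 0.8.

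**4. Relaxing equal SDs.** If the final SD is k times the baseline SD, the slope is kρ and the variance ratio is k²(1 − ρ²)/(1 + k² − 2kρ). At 64 per group:
- k = 1.1: power is 87.4% (ρ = 0.5), 83.3% (0.7), 81.4% (0.8) and 80.2% (0.9).
- k = 1.2: power is 85.3% (ρ = 0.5), 81.5% (0.7) and 80.3% (0.8, where the slope is 0.96).

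The gain shrinks as the slope approaches 1. In none of these cases does ANCOVA fall below the t test.

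**5. Chance baseline imbalance, at ρ = 0.7 and equal SDs.**
- Implied HbA1c SD = 0.686/√(2 × 0.3) = 0.89.
- SE of the baseline difference = 0.89 × √(2/64) = 0.157 points.
- An imbalance of one SE shifts the change-score estimate by (1 − 0.7) × 0.157 = 0.047 points, which is 14% of the planned 0.34.

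**The case against.** The strongest reply is that nothing here is invalid. One endpoint, one test and one alpha are fixed in advance; the sample size matches that test; and the change-score t test is unbiased with correct type I error under randomisation. All of this stands, and it is why the point concerns lost precision rather than an invalid primary test.

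Second, the size of the gain rests on an unknown correlation and on equal SDs. Entry requires HbA1c above 6.5%, with no such limit at 90 days, so the baseline SD may well be the smaller one. That also stands: the gain could be 2 points or less. It is still not a loss.

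Third, the 52-per-group figures depend on reading 130 as the number enrolled, against section 4.3. The reading is possible but separate, and the conclusion does not need it.

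Fourth, a shift of 0.047 is under half the SE of the treatment effect (0.686 × √(2/64) = 0.12) and is already contained in the t test's standard error. This is correct. It is avoidable noise, not bias.

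Fifth, the conditional model is labelled exploratory and cannot replace the primary test, and no p-value threshold is written. The label does limit the harm. It does not remove the dependence: the text ties the model to the primary outcome's result, and leaving the trigger unstated makes selective use easier.

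**Conclusion.** The concern holds. The protocol makes an unadjusted t test primary, although the model it later describes already includes baseline HbA1c, and it makes that model depend on the primary result.

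At 64 per group, effect 0.50 and equal SDs, the cost is about 10 power points at ρ = 0.5, 6 at 0.7 and 2 at 0.9. Put as sample size, that is 15 to 3 fewer patients per group for 80% power. With a larger final SD the gain can fall to almost nothing. The correlation and the SD ratio are my assumptions.

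The result-dependent wording is a defect whatever their values. Since the t test is valid and adequately powered on the plan's own terms, this is a change that should be made, not one on which the trial's validity depends.

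**What to change.** In section 4.6:

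- Make the primary analysis an ANCOVA of 90-day HbA1c on treatment group with baseline HbA1c as covariate, two-sided at 0.05, reporting the adjusted difference with its 95% confidence interval.
- Keep the t test on change as a supportive analysis.
- Delete the clause that makes the regression depend on the primary result. Name its socioeconomic and clinical covariates in advance and run it in every case as exploratory.
- For consistency, use the same baseline-adjusted form for the continuous secondary outcomes, which remain exploratory.

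The cost is a sentence or two. No new data or patients are needed. The sample size in section 4.3 can stay as it is and becomes conservative if the baseline slope differs from 1.

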##### Secondary outcome

4.1.2.2

After 3 months of use of the received capsules (cinnamon or placebo), the following secondary outcomes will be collected:

(1)Reduction of lipid levels (LDL cholesterol, triglycerides and total cholesterol);(2)Increase HDL cholesterol levels.(3)Reduction of anthropometric measurements (weight, waist circumference, waist circumference, neck circumference, thigh circumference, hip circumference, body mass index, central adiposity index, neck-thigh ratio, waist-hip ratio, waist-thigh ratio, waist-to-height ratio).

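### Triglycerides are to be compared by an unadjusted t test with no transformation: valid, but inefficient if the values are right-skewed, and a baseline-adjusted log-scale model would cost only a change of wording

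*Protocol article*

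**What the plan says.** Section 4.6 (Statistical analysis) begins its paragraph on secondary outcomes with "Secondary analyses will include means tests" and sets one method for the whole class: "means tests (*t* test) for numerical secondary variables". Section 4.1.2.2 (Secondary outcome) lists "Reduction of lipid levels (LDL cholesterol, triglycerides and total cholesterol" as its first item, so triglycerides fall under that rule. Lipid lowering is also in the general objective (3.1) and is specific objective 2 (3.2).

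No transformation is named, and nothing is said about what a skewed distribution would change. Change from baseline is defined as the analysed quantity for HbA1c only; for lipids the article does not say whether change or final value is tested. Adjustment for the initial value appears only in an exploratory regression of final HbA1c.

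The article limits the weight of these tests. It says "Although we continue to use the significance level of 0.05, these tests will be interpreted with caution", because "the study was not designed to have statistical power for all of these tests", and adds "These tests will be considered exploratory".

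**The concern.** Triglycerides cannot be negative and are plausibly right-skewed, although the article does not describe their distribution. If they are skewed, a few high values inflate the SD of the raw values and of the raw change. A two-sample t test then has less power, and gives a wider interval, than a comparison on the log scale.

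The same t test also leaves most of the baseline information unused. A final-value comparison ignores baseline altogether, and a change score subtracts it with a fixed weight of one instead of an estimated slope.

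At stake is precision on a named lipid outcome in a trial sized for something else. The measurements needed for a sharper estimate are already in the schedule.

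**Working it through.** **The plan's own figure.** Section 4.3 states "if we consider the effect of 0.50, we need 64 participants per group (128 total) for 80% power" and "The calculations were made in GPower 3.0 by choosing the *t* test for independent samples". Reading the printed 0.722 and 0.652 as 0.72² and 0.65², d = 0.34 / √((0.72² + 0.65²)/2) = 0.4957. With d = 0.50 and two-sided alpha 0.05, the noncentral t gives power 0.801 at 64 per group. The figure reproduces, but it concerns HbA1c; no such figure is given for triglycerides.

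**Inputs.** From the article: 130 participants at the end, 1:1 allocation (65 per arm), alpha 0.05. Assumed: two-sided testing, lognormal values, log SD (σ) 0.4 to 0.6, pre-post correlation (ρ) 0.5 to 0.7, and a proportional reduction of 15% or 5%.

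**Closed form on the log scale.** The effect is δ = ln(1 − reduction), and SE = √(v × 2/65). The variance v is σ² for the final value, 2σ²(1 − ρ) for change, and σ²(1 − ρ²) for the final value adjusted for baseline. So the adjusted variance is (1 + ρ)/2 of the change variance (0.75 at ρ = 0.5, 0.85 at ρ = 0.7). It is 1 − ρ² of the final-value variance (0.75 and 0.51).

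Example: σ = 0.5, ρ = 0.5, 15% reduction, |δ| = 0.1625.
- Log change: SE = 0.5 × √(2/65) = 0.0877; power ≈ Φ(1.853 − 1.96) ≈ 0.46.
- Adjusted: SE = 0.5 × √0.75 × √(2/65) = 0.0760; power ≈ Φ(2.14 − 1.96) ≈ 0.57.

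**Simulation.** The raw-scale tests have no simple closed form, so all five analyses were simulated (bivariate lognormal, 65 per arm, 20,000 runs per setting). Power in % for a 15% reduction:

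| σ, ρ | Raw change | Log change | Raw final | Log final | Log final adjusted for log baseline |
|---|---|---|---|---|---|
| 0.4, 0.5 | 54.4 | 63.0 | 59.9 | 63.3 | 74.9 |
| 0.4, 0.7 | 75.9 | 84.5 | 59.5 | 62.7 | 89.5 |
| 0.5, 0.5 | 37.1 | 45.3 | 41.2 | 45.2 | 56.2 |
| 0.5, 0.7 | 53.7 | 65.8 | 41.6 | 45.5 | 72.5 |
| 0.6, 0.5 | 25.7 | 34.0 | 29.1 | 33.2 | 42.4 |
| 0.6, 0.7 | 37.5 | 50.7 | 29.3 | 33.5 | 57.1 |

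Differences read from the table, in points:
- Adjusted log model minus raw change: 13.6 to 20.5 (about 14 to 20).
- Adjusted log model minus raw final: 13.3 to 30.9 (about 13 to 31).
- Log scale alone, change scores: 8.2 to 13.2 (about 8 to 13).
- Log scale alone, final values: 3.2 to 4.2. A separate run at 64 per arm gave up to 4.7, so about 3 to 5.
- Baseline covariate, once on the log scale: 5.0 to 11.9 over log change and 9.2 to 27.0 over log final.

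**Smaller effect.** For a 5% reduction the adjusted model gains about 1 to 3 points over raw change and 1 to 7 over raw final. At σ = 0.4, ρ = 0.7, the powers are 14.5% (raw change), 10.7% (raw final) and 17.7% (adjusted). At σ = 0.6, ρ = 0.5, they are 7.0%, 7.2% and 8.4%.

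**Type I error.** With no effect, rejection was 4.8% to 5.4% for all five analyses.

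**Shape of the effect.** The direction does not need a proportional effect. With a constant 15 mg/dL fall from a median of 150 (64 per arm, σ = 0.4, ρ = 0.5), power was 24% for raw change and 35% for log change.

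**The case against.** The strongest reply is that nothing here is wrong. Section 4.6 names a test and no scale; a t test on log values is still a t test, and the wording does not shut out other analyses. Descriptive tables and plots of all variables are planned, where skewness would show. Transforming one laboratory variable is ordinary content for a statistical analysis plan, which may exist and is not to hand. The secondary tests are declared exploratory and unpowered, and a mean difference in mg/dL is a legitimate target.

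Much of this stands. The raw scale and the skewness are inferences. The point is therefore not an omission, a contradiction or a miscalculation. What remains is that one method is stated for the whole class of outcome, and a better use of the same data is available whichever scale or quantity was meant. Even on log values, an unadjusted comparison gives up 5 to 27 points in the table above. The exploratory label limits what may be claimed; it is no reason to prefer a less precise estimate.

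Two stronger readings are tempting. A reader might infer that the t test is invalid for skewed data; the simulated type I error does not support that. A reader might also take 8 to 13 points as the known cost of working on the raw scale. That range assumes change scores and a 15% effect, and the article fixes neither for triglycerides. With final values the scale alone costs 3 to 5 points, and with a 5% effect about 2 points or less. Other assumptions about spread and effect carry the scale-only loss anywhere from about 1 to 23 points.

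**Conclusion.** The point holds as a minor efficiency improvement. The stated t test controls type I error but is inefficient for triglycerides if they are right-skewed. Under the assumptions above, a baseline-adjusted log-scale model gains about 14 to 20 points of power over raw change and 13 to 31 over raw final values at a 15% reduction, falling to about 1 to 7 at 5%. Not knowing whether change or final value is meant alters the size of the gain but not its direction. Much of the gain comes from the baseline covariate and should not be credited to the log scale.

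Every power figure rests on assumed spread, correlation, effect and lognormal shape, because the article supplies none of these for triglycerides. The primary HbA1c analysis and the sample size are untouched. The conclusion should not be stretched to HOMA-IR, which is calculated as a laboratory index (4.1.1.5) but is not a listed outcome.

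**What to change.** In section 4.6, or in the statistical analysis plan before unblinding, state that triglycerides are analysed by a linear model of the log final value on treatment arm and log baseline value. Report the effect as a ratio of geometric means with its 95% CI, and keep the exploratory label. Naming the scale in advance also avoids choosing a transformation after seeing the results.

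The cost is one sentence. No further participants, visits or measurements are needed. The small downside is that the effect is read as a percentage and not as a difference in mg/dL; arm-level summaries in mg/dL can still be shown alongside.
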